### Discontinuing or modifying interventions

Arms will be discontinued (or modified to remove the risk) if there is evidence that they are harming exposed individuals. We note that only low/negligible-risk service modifications will be tested. Risk will be assessed at the intervention selection stage by a group of researchers, programme managers and lay representatives. Interventions that are deemed to be appropriate will also be independently reviewed by independent ethics committees in each setting before they are implemented in the platform trial.

There are no *a priori* strategies to improve adherence as we are not prespecifying the interventions.

As our trials will be embedded within routine service delivery, we cannot exclude the possibility that other initiatives will be introduced by local teams before, during or after individual trials. We will report all programmatic changes that take place during individual trials that could bias our findings.

### Outcomes

This platform trial focuses on testing interventions that improve equitable access to eye services among those identified with a need during screening. We will use attendance as a proxy for access. Our analysis focuses on the population groups found to have the lowest attendance at baseline.

#### Primary outcome

The proportion of people attending triage clinic on their appointed date from the left-behind group was measured using attendance data collected by staff when people check-in.

The left-behind group will be identified at baseline as part of the ‘identify’ stage of the IM-SEEN process. This group will be constituted of the group(s) with the lowest baseline attendance rates that collectively constitute at least 10% of the total population. A focus on left-behind groups is important to programme managers who are trying to close gaps, extend health service coverage and ensure that their services do not exacerbate existing inequalities.

When referred participants check-in at ophthalmic clinics, their attendance status is recorded by administrative staff using the Peek app, which automatically updates a central database that holds records of each participant’s eye care need, sociodemographic characteristics, arm allocation and attendance status at the ophthalmic clinic on the appointed date. Our Bayesian algorithm will review the attendance data for every referred participant every 72 hours and calculate the probability of attendance within each arm. In our modelling, we have estimated that 100 people will be referred every 72 hours. This aligns with what we have observed in India and Kenya where approximately 1000 people are screened per day, of whom approximately one-third are referred. We have stipulated that the left-behind group will include at least 10% of the total population (ie, 100 people every 72 hours). In programmes where fewer people are referred every 72 hours, the interim analysis window will be extended as appropriate.

#### Secondary outcome

The proportion of people attending triage clinic on their appointed date across the entire population was measured using attendance data collected by staff when people check-in.

If an intervention is found to increase attendance among the left-behind group, we also want to check whether there has been an impact on the overall mean attendance rate. This is to hedge against adopting an intervention that improves access for the left-behind group but leads to a large overall fall in attendance across the entire programme. We will use absolute percentage differences in attendance for comparisons between the left-behind and general populations exposed to the intervention.

### Participant timeline

This platform trial is embedded within routine screening programmes. From the individual participant perspective, they will flow through the screening programmes as normal; participants will present and have their eyes checked by a first-line screener either in their own home, at a school, local clinic or community meeting place, depending on the setting. The screener will ask a series of sociodemographic questions and perform a ‘tumbling E’ visual acuity assessment, all using the Peek smartphone app. Those who screen positive will be referred to a local triage centre where their eyes will be rechecked by a more highly skilled practitioner and treatment will be delivered. Those requiring more advanced care will be referred on to the appropriate service provider.

Some programmes use a roaming team of screeners who visit communities sequentially. Others train screeners who remain in one location. Table 3 summarises the two approaches.

**Table 3 T3:** Different screening programme approaches

	Outreach screening model	Primary care screening model
Community-based screening	Outreach screeners trained to use the Peek app attend schools/local venues and screen those who are present before moving to the next location	Primary care staff are trained to use the Peek app to opportunistically screen and refer those who present to primary care
Referral to triage	Those who screen negative (ie, with no eye health need) are discharged. Those who screen positive provide their contact details and answer a series of socioeconomic questions. They are then referred to triage.	
Triage, basic treatment and further referral	An ophthalmic nurse checks-in attenders using the Peek app and then performs an eye examination. Simple treatments are provided for basic issues (eg, eye drops for conjunctivitis). Other cases are referred for refraction and/or further care. Referral status is recorded in the Peek app.	
Specialist treatment	A receptionist checks-in those who present to receive refraction or further ophthalmic treatment using the Peek app at the secondary or tertiary clinic.	

In some settings, triage will be co-located with screening. In others, it will be co-located with the provision of refractive services, and in others, it will be co-located with refraction and all other specialist treatment providers, that is, in a hospital. Online supplemental figure S2 shows the three different configurations of screening, triage and treatment.

Most programmes aim to progress to a model of co-locating triage with screening or treatment in order to reduce the appointment burden on participants and minimise loss-to-follow-up. In the former case, participants testing positive at screening are ‘referred’ to a room next door for triage. In the latter case, they are given an appointment to attend a central triage and treatment clinic, commonly 1–2 weeks after screening. In most programmes, SMS reminders are sent on the date of referral and the day before the appointment. Interventions will be allocated by the algorithm at the point of referral.

### Sample size

As we are using stopping rules, we will not prespecify a minimum sample size or estimate effect sizes for the intervention arms. Instead, participants will be continually recruited until we reach a predetermined maximum sample size or sufficient data accrue to trigger one or more of the other stopping rules. Trialists have argued that this approach is more ‘efficient, informative and ethical’ than traditional fixed-design trials as this approach optimises the use of resources and can minimise the number of participants allocated to ineffective or less effective arms.^17^ Every 72 hours, the algorithm will review the attendance data and calculate the probability of attendance within each arm.

#### Operating characteristics for individual trials of interventions administered to individual participants

Based on extensive scenario modelling, we have decided to use the following stopping rules for individual trials that test interventions administered to individuals (rather than clusters):

There is a >x% probability that one arm is best that is, there is a >0% difference between the arms (default x=95%)There is a >y% probability that the difference between the best arm and the arms remaining in the trial is <1% (Default y=95%)

Individual trials may include a third ‘ceiling’ stopping rule around a maximum length of time that the trial will run for, or a maximum sample size, depending on the context. For instance, there may only be funding to run a particular service modification for 12 months, or there may only be capacity to trial a new intervention for the first 10 000 people. The default ceiling will be 10 000 participants.

Each individual trial will end once one or more of the stopping rules has been met. At that point, the superior arm will become the new standard care in the programmes(s) where it was tested. The overall platform trial will be stopped once attendance reaches or exceeds 80% for every sociodemographic group in a given site. Figure 3 provides a visual representation of how the trial will run, including the point at which new interventions can be added.

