**Trial registration number:**

ISRCTN53970958.

STRENGTHS AND LIMITATIONS OF THIS STUDYRandomised controlled trials are resource intensive and often require lengthy set up periods. The adaptive platform design allows for the evaluation of multiple interventions with a single outcome, governed by a predefined set of criteria.The study defaults are designed to test multiple low-risk, incremental service modifications in series, and quickly identify those that are just as good as, or superior to the status quo.Our high default tolerance for type I error means that we will often incorrectly identify arms as superior when really there is no difference. This is acceptable when arms confer similar costs and negligible risks.Our default very low type II error rate means that we will very rarely mistakenly identify an inferior arm as being superior.Our trial is embedded within screening programmes and uses automated randomisation, allocation, data collection and statistical testing to minimise resource requirements.

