Box 2Programme management teamThe platform trial infrastructure is being set up by the IMprovement Studies for Equitable and Evidence-based iNnovation (IM-SEEN) collaborators, comprised of LSHTM, Peek Vision, COESCA, Kenyan MoH, University of Botswana, NNJS and [name] Eye Hospital using Wellcome Trust and NIHR funds, and in collaboration with national eye care administrators. Decisions around which interventions to test will be made by a multistakeholder group that includes the screening programme funders, implementing partners and community representatives, with support from LSHTM statisticians. Once the first few interventions have been tested, it is anticipated that the local programme management teams will assume total responsibility for the platform trial process in each country, led by the relevant national decision-makers with responsibility for funding and administering the screening programme in collaboration with local lay representatives and programme implementers. Our ultimate aim is that the broader IM-SEEN process of gathering sociodemographic data, engaging with left-behind groups, identifying interventions, and testing them can be taken to scale across many different sites and services, and that as the approach matures, an increasing number of decisions can be delegated from senior managers to local programme implementers.

All interventions felt to present any more than minimal risk to participants will be excluded. An explicit trade-off discussion will be held around the maximum financial resources that can be released to fund the testing of one or more intervention (which carries an opportunity cost in terms of the number of people who can be screened) and the minimum ‘meaningful’ improvement that would be required to justify this expenditure. For instance, the local management group may be willing to screen 1% fewer people if attendance rates in the worst-off group improved by >5%. This decision directly informs the next step: agreeing the stopping rule thresholds for the trial (‘x’, ‘y’, and ‘n’ in the three rules below):

There is a >**x**% probability that one arm is best.There is a >**y**% probability that the difference between the arms remaining in the trial is <1%.(Optional), a maximum of **n** people have been recruited.

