**Figure 3 F3:**
[figure not shown]
Platform trial schematic.

We conducted simulations to estimate the impact of the early stopping rules on error rates and sample sizes. For both rules, 95% threshold values were used as default. We assumed a fixed 1:1 ratio for two-arm trials where the control arm had 50% outcome rate and the intervention arm has an effect difference of d, ranging from 0% to 5%. A total of 1000 simulations were conducted for each value of d, and we assumed that interim analysis would take place for every 100 outcomes observed.

In this trial, we prioritise high statistical power (1−β). Minimising β will protect against the risk of incorrectly identifying an inferior arm as a winning arm. Simulation results show that the expected power in our trial will be at least 98% when an intervention arm is more effective than the control arm by a difference of 3% or greater. When the winning arm is only marginally more effective by a difference of 1%, our trial will still ensure a statistical power of 92%, which is greater than the power of 80% used in most conventional trials. It is noted that the high statistical power in our trial comes at the cost of increased chance of committing type I error. Furthermore, it will take longer to run the trial to find smaller differences. When there is no difference between arms, we expect 32% chance of making false-positive conclusions (online supplemental table S1). But we will treat the risk of committing type I error as not a major concern because we expect no or minimal harm in selecting either of the two arms with equal effectiveness.

The values of posterior probabilities specified in rules 1 and 2 will be determined by our research team at the start of each individual trial. The default values will be 95% as above, however, it might be appropriate to use lower thresholds for interventions where the costs and risks are negligible, and higher thresholds when the costs and/or risks are high. For example, to decrease the chance of committing type I errors, the probability threshold in rule 1 will be increased from 95% to a higher value (figure 4).

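### At the default settings, stopping rule 2 (95% probability of a difference under 1 point) cannot be met before the 10 000 ceiling at 30%–50% attendance

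*Protocol article*

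**What the plan says.** The section on operating characteristics for individually administered interventions gives two stopping rules. Rule 1 stops on a posterior probability above 95% that one arm is best. Rule 2 stops on more than 95% "probability that the difference between the best arm and the arms remaining in the trial is" below 1%. The list of rules under Interventions and administration words rule 2 slightly differently, as the "probability that the difference between the arms remaining in the trial is <1" percent. There x, y and n are left as letters to be chosen for each trial, while the 1% margin is written in as a fixed number.

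A trial may add a "stopping rule around a maximum length of time that the trial will run for, or a maximum sample size, depending on the context". "The default ceiling will be" 10 000 participants, and the Abstract lists that figure with the other default stopping rules.

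The strengths and limitations box says the defaults are designed to test low-risk modifications in series and "quickly identify those that are just as good as, or superior to the status quo".

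**The concern.** Rule 2 is the only rule that lets a trial conclude that its arms do not differ materially. A 1-point margin is narrow for a comparison of two proportions near one half, and 5000 per arm may not be enough to place the difference inside it with 95% probability. If so, one of the default rules can never operate under the default ceiling. A trial of equivalent arms then has only two exits: rule 1 names a winner, or the trial recruits to the ceiling and closes without a conclusion. Every individually randomised trial that keeps the defaults, in all four countries, would inherit this.

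**Working it through.** **Inputs.** Margin 1 point, y = 95%, ceiling 10 000 (operating characteristics section). Two arms 1:1 and a look every 100 outcomes (same section: "We assumed a fixed 1:1 ratio for two-arm trials where the control arm had 50% outcome rate"). Attendance 30%–50% (Abstract). Prior beta(100,100) per arm (Statistical methods).

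**The plan's own figures first.** The article reports 32% false positives with no difference, 92% power at 1 point and at least 98% at 3 points or more. The text shown gives neither the ceiling simulated nor how often rule 2 ended a trial. I simulated two beta-binomial arms with these priors and a 10 000 cap, looking every 100 outcomes in total or per arm. Rule 1 named a winner in 37–42% of equal-arm trials. It chose the better arm in 45–48% at 1 point and 94–95% at 3 points. The stated 92% and 98% appear only if power means one minus the chance of declaring the worse arm (92–93% and 98–99%). The 32% is approached with a 5000 cap, or with effectively no cap if winners are counted in one direction only (30–31%). The source of the stated figures is therefore not unique. Nothing below depends on it.

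**Step 1: posterior SD at the ceiling.** With n = 5000 per arm, attendance p and observed difference 0, the posterior mean in each arm is m = (np + 100)/(n + 200). The SD of the difference is sqrt(2m(1−m)/(n + 201)). At 50%: sqrt(2 × 0.25/5201) = 0.0098, or 0.98 points.

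**Step 2: highest attainable probability.** An observed difference of 0 is the most favourable case. Two-sided, the maximum is 2Φ(0.01/SD) − 1. One-sided (leader minus other below 1%), it is Φ(0.01/SD).

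| Attendance | m | SD (points) | Two-sided maximum | One-sided maximum |
|---|---|---|---|---|
| 50% | 0.500 | 0.98 | 0.69 | 0.85 |
| 40% | 0.404 | 0.96 | 0.70 | 0.85 |
| 30% | 0.308 | 0.91 | 0.73 | 0.87 |

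All are below 0.95. The maximum rises with n, so no earlier look can do better.

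**Step 3: participants needed.** Two-sided: n + 201 = 2m(1−m)(1.96/0.01)².
- At 50%: 0.5 × 38 416 = 19 208, so n = 19 007 and the total is about 38 000.
- At 30% (m ≈ 0.3025 at that size): 0.422 × 38 416 ≈ 16 210, so n ≈ 16 010 and the total is about 32 000.

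One-sided, with 1.645 in place of 1.96, the totals are about 26 700 and 22 500.

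**Step 4: what happens to equal arms.** With the 10 000 cap, rule 2 fired in 0 of 4000 simulated trials at each of 30%, 40% and 50%, under both the two-sided and the leader-minus-other readings. At 50%, about 41% ended with a winner and about 59% at the ceiling, with a median size of 10 000.

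**Step 5: other readings of the inputs.**
- A flat prior gives 0.68 at 50%.
- If 10 000 were meant per arm, the maximum is 0.85–0.88.
- If 10 000 counts all recruits and only 10% are in the left-behind group (500 per arm), it is about 0.3.
- At 80% attendance, the level at which the platform closes, it is 0.79.
- More than two arms leave fewer per arm and lower it further.
- Under the cap, rule 2 becomes reachable only near 5% or 95% attendance.

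**The case against.** **The settings are adjustable.** The ceiling is optional, and x and y are chosen for each trial, with lower values foreseen for very low-cost, low-risk interventions. This stands, and it limits the point to the defaults. With the 1-point margin and the same cap, lowering y to 60% or 51% made rule 2 fire in 48% or 60% of equal-arm runs. Without a cap it stopped about 38–40% of them, but only at about 38 000 participants. That is more than some sites could supply. If the one-third referral rate reported for India and Kenya is assumed throughout, a site of 50 000–70 000 people yields about 16 700–23 300 referrals. A reader might infer that equal arms can never be declared equal in any trial on the platform; the documents do not support that.

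**Naming a winner between equal arms is accepted.** The article says so openly, on the ground that choosing either arm does minimal harm. A reader might infer that the unreachable rule 2 causes these winners. It does not: the rate is about 41% with a 1-point margin and 40–41% with 2.5 points.

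**An undecided end is foreseen.** The ceiling exists to close indeterminate trials. True, but this does not square with the claim that the defaults find equally good arms quickly.

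**Rule 2 might mean that no remaining arm beats the leader by 1%.** It would then fire before 10 000 in 83–88% of equal-arm runs. Neither wording says this, and it does not match the reported figures. Rule 1 would name a winner in only about 4% of equal-arm runs, against the stated 32%. At 1 point the better arm would lead at stopping in about 76–77%, against 92%.

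**Supplementary table S1 and figure 4 are not shown.** They may state the ceiling simulated, so nothing can be inferred about what the authors overlooked. The arithmetic is unaffected.

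**Conclusion.** The point holds for the default combination of y = 95%, a 1-point margin, a 10 000 ceiling and two arms 1:1, at the attendance the article reports. Rule 2 then has no route to firing: its probability cannot exceed 0.69–0.73 (0.85–0.87 one-sided), and it needs roughly three to four times the ceiling (more than twice, one-sided). The consequence is wasted recruitment and missing conclusions: about 59% of equal-arm trials at 50% attendance use all 10 000 participants and end undecided. It is not a greater risk of adopting a worse arm. The ceilings on the probability are arithmetic from the stated defaults; the 59% and 41% rest on simulation with looks every 100 outcomes. Because y and the ceiling can be reset for each trial, this is a should-fix.

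**What to change.** In the operating characteristics section, add a set-up requirement: at the expected attendance and number of arms, the posterior probability that the difference lies within the margin must be able to exceed y at the ceiling n when the observed difference is 0. Add the margin to the values the management group chooses. If the check fails, the group changes the margin (to the largest difference it regards as immaterial), y or n, with simulated consequences in front of it.

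For two arms at 50% attendance, changing one setting alone, the bare limits are a margin above 1.96 × 0.98 = 1.92 points, y below 0.69, or n of about 38 000.

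No margin is costless. As an illustration, at 10 000 and 50% attendance a 2.5-point margin passes the check (2Φ(0.025/0.0098) − 1 = 0.99). Rule 2 then fires in about 55–57% of equal-arm trials and median size falls to 6000. Correct selection at 3 points moves only from 95% to 94%. But about 41% of true 1-point gains, and 17–18% of true 2-point gains, would be labelled as no material difference. A reader might take 2.5 points as the right value; nothing in the article supports treating that difference as immaterial on a platform that seeks marginal gains.

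If the current defaults are kept, state that rule 2 is inoperative under the default ceiling, and qualify the claim in the strengths and limitations box about finding arms that are as good as the status quo. Either way, report the ceiling used in the simulations and how often each rule ends a trial. The cost is a few sentences and a short calculation for each trial, which the statistician already advising on thresholds can supply.

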**Figure 3 F3:**
[figure not shown]
Platform trial schematic.

We conducted simulations to estimate the impact of the early stopping rules on error rates and sample sizes. For both rules, 95% threshold values were used as default. We assumed a fixed 1:1 ratio for two-arm trials where the control arm had 50% outcome rate and the intervention arm has an effect difference of d, ranging from 0% to 5%. A total of 1000 simulations were conducted for each value of d, and we assumed that interim analysis would take place for every 100 outcomes observed.

In this trial, we prioritise high statistical power (1−β). Minimising β will protect against the risk of incorrectly identifying an inferior arm as a winning arm. Simulation results show that the expected power in our trial will be at least 98% when an intervention arm is more effective than the control arm by a difference of 3% or greater. When the winning arm is only marginally more effective by a difference of 1%, our trial will still ensure a statistical power of 92%, which is greater than the power of 80% used in most conventional trials. It is noted that the high statistical power in our trial comes at the cost of increased chance of committing type I error. Furthermore, it will take longer to run the trial to find smaller differences. When there is no difference between arms, we expect 32% chance of making false-positive conclusions (online supplemental table S1). But we will treat the risk of committing type I error as not a major concern because we expect no or minimal harm in selecting either of the two arms with equal effectiveness.

The values of posterior probabilities specified in rules 1 and 2 will be determined by our research team at the start of each individual trial. The default values will be 95% as above, however, it might be appropriate to use lower thresholds for interventions where the costs and risks are negligible, and higher thresholds when the costs and/or risks are high. For example, to decrease the chance of committing type I errors, the probability threshold in rule 1 will be increased from 95% to a higher value (figure 4).

